## Abstract

**Introduction:**

Multimorbidity and polypharmacy are major risk factors for potentially inappropriate prescribing (eg, overprescribing and underprescribing), and systematic medication reviews are complex and time consuming. In this trial, the investigators aim to determine if a systematic software-based medication review improves medication appropriateness more than standard care in older, multimorbid patients with polypharmacy.

**Methods and analysis:**

Optimising PharmacoTherapy In the multimorbid elderly in primary CAre is a cluster randomised controlled trial that will include outpatients from the Swiss primary care setting, aged ≥65 years with ≥three chronic medical conditions and concurrent use of ≥five chronic medications. Patients treated by the same general practitioner (GP) constitute a cluster, and clusters are randomised 1:1 to either a standard care sham intervention, in which the GP discusses with the patient if the medication list is complete, or a systematic medication review intervention based on the use of the 'Systematic Tool to Reduce Inappropriate Prescribing'-Assistant (STRIPA). STRIPA is a web-based clinical decision support system that helps customise medication reviews. It is based on the validated ‘Screening Tool of Older Person’s Prescriptions’ (STOPP) and ‘Screening Tool to Alert doctors to Right Treatment’ (START) criteria to detect potentially inappropriate prescribing. The trial’s follow-up period is 12 months. Outcomes will be assessed at baseline, 6 and 12 months. The primary endpoint is medication appropriateness, as measured jointly by the change in the Medication Appropriateness Index (MAI) and Assessment of Underutilisation (AOU). Secondary endpoints include the degree of polypharmacy, overprescribing and underprescribing, the number of falls and fractures, quality of life, the amount of formal and informal care received by patients, survival, patients’ quality adjusted life years, patients’ medical costs, cost-effectiveness of the intervention, percentage of recommendations accepted by GPs, percentage of recommendation rejected by GPs and patients’ willingness to have medications deprescribed.

**Ethics and dissemination:**

The ethics committee of the canton of Bern in Switzerland approved the trial protocol. The results of this trial will be published in a peer-reviewed journal.

**Trial registration numbers:**

Clinicaltrials.gov (NCT03724539), KOFAM (Swiss national portal) (SNCTP000003060), Universal Trial Number (U1111-1226-8013).

Strengths and limitations of this studyThe Optimising PharmacoTherapy In the multimorbid elderly in primary CAre (OPTICA) trial is the first randomised controlled trial to examine the effect of the 'Systematic Tool to Reduce Inappropriate Prescribing'-Assistant, a software-assisted clinical decision support tool, on medication appropriateness in older, multimorbid patients with polypharmacy in a primary care setting.OPTICA is the first randomised controlled trial to test the use of software-based structured medication reviews in Swiss primary care.The OPTICA trial demonstrates how linked and coded data from electronic medical records can be used to evaluate primary care interventions in a randomised controlled trial setting. The investigators limit selection bias by using screening lists with a random sample of potentially eligible patients and randomising general practitioners (GPs) after patient recruitment is complete, but cannot eliminate the risk of selection bias.The investigators chose a sham intervention in accordance with usual care in the control group to improve patient blinding but, by design, they could not blind GPs.

## Introduction

Globally, there is a high prevalence of multimorbidity and polypharmacy in people more than 65 years old.^1 2^ Multimorbidity is commonly defined as the coexistence of three or more chronic diseases,^3^ and polypharmacy is commonly defined as the regular intake of five or more medications.^4^ Polypharmacy is often caused by multimorbidity and is linked to a high risk of potentially inappropriate prescribing,^5 6^ which has three main elements, namely: (1) overuse, (2) underuse and (3) inappropriate use of medications (ie, wrong dose/medication for the indication).^7^

Appropriate polypharmacy denotes a situation in which ‘medication use is optimised according to the patients’ clinical needs’ and in which patients ‘receive the most appropriate combinations of medications based on the best available evidence’.^8^ While appropriate polypharmacy can improve quality of life and prevent consequences of disease, inappropriate polypharmacy can harm patients’ health.^4^ For instance, it can increase the risk of falls and fractures,^9^ lead to cognitive decline,^10 11^ and it can reduce quality of life.^9^ Polypharmacy also increases the risk of drug–drug interactions, drug–disease interactions and adverse drug events.^12–15^ Treatment of older patients with multimorbidity and polypharmacy is a complex problem in primary care and other medical fields and both conditions are increasingly common as populations age. Due to the relatively small number of randomised controlled trials on different interventions for the management of multimorbid people, there currently remain uncertainties about the effectiveness of these interventions.^16^ Medication reviews in older adults with multimorbidity and polypharmacy can be complicated and time-consuming.^17^ General practitioners (GPs) have reported that time limitations and lack of user-friendly and reliable tools pose significant barriers to regular medication optimisation activities in practice.^18^

Current evidence is ambiguous on whether review interventions that aim at optimising medication can reduce inappropriate polypharmacy. A systematic review and meta-analysis of short-term medication review interventions published in 2017 showed that such isolated medication reviews have an impact on drug-related outcomes, but only minimally influence clinical outcomes and have no impact on quality of life.^19^ A more recent systematic review and meta-analysis on interventions to improve the appropriateness of medication use in older people showed that such interventions may be beneficial for reducing potential prescribing omissions, but that it remains uncertain whether they improve the appropriateness of medication use.^20^

The increasing use of electronic medical records (EMR) and electronic prescribing has opened opportunities to incorporate web-based clinical decision support systems (CDSS) at the point of care. For instance, a complex intervention with an informatics tool and financial incentives has led to a reduction in high-risk prescribing of non-steroidal anti-inflammatory drugs and antiplatelet medications.^21^ Medication optimisation studies that use CDSS enabled by electronic medical records have shown that the interventions are feasible and acceptable to clinicians, but evidence that they lead to more appropriate use of medications in general and improve clinical outcomes is still limited.^22^

### Objectives

The primary aim of the cluster-randomised ‘Optimising PharmacoTherapy In the multimorbid elderly in primary CAre’ (OPTICA) trial is to test whether the use of a systematic, software-assisted medication review intervention leads to a more appropriate use of medications than a usual care sham intervention. This primary outcome will be measured by the Medication Appropriateness Index (MAI) and the Assessment of Underutilisation (AOU). Secondary outcomes are the degree of polypharmacy, the degree of overprescribing, the degree of underprescribing, the number of falls and fractures, quality of life, the amount of formal and informal care received by patients, survival, patients’ quality adjusted life years (QALYs), patients’ medical costs, cost-effectiveness of the intervention, percentage of recommendations accepted and rejected by GPs, and patients’ willingness to have medications deprescribed.

## Methods and analysis

### General study design and setting

The OPTICA trial is a cluster randomised controlled trial (RCT), coordinated at the Institute of Primary Healthcare of the University of Bern (BIHAM). Participating GPs, who will each systematically recruit multimorbid, older patients with polypharmacy, define the clusters. Through randomisation, the GPs will be allocated to the structured medication review or a usual care based sham intervention.

The investigators used the Standard Protocol Items: Recommendations for Interventional Trials (SPIRIT) checklist when they wrote this protocol.^23^ Please refer to figure 1 for the study flow chart and figure 2 for a description of the data flow within the OPTICA trial.

**Figure 1 F1:**
[figure not shown]
OPTICA trial flow chart. Flow diagram of the progress through the phases of the OPTICA trial. In dark grey: steps done by general practitioners. In white: steps done by study team at BIHAM. *Target number. BIHAM, Institute of Primary Healthcare of the University of Bern; GPs, general practitioners; OPTICA, Optimising PharmacoTherapy In the multimorbid elderly in primary CAre; STRIPA, Systematic Tool to Reduce Inappropriate Prescribing-Assistant.

**Figure 2 F2:**
[figure not shown]
OPTICA data flow chart. Step-by-step explanation of the data flow during the OPTICA trial. EMR, electronic medical record; FIRE, Family medicine ICPC Research using Electronic medical records; GPs, general practitioners; OPTICA, Optimising PharmacoTherapy In the multimorbid elderly in primary CAre; STRIPA, Systematic Tool to Reduce Inappropriate Prescribing-Assistant.

### Cluster definition

The trial will be conducted in about 40 primary care offices in the German-speaking regions of Switzerland. Each participating GP, who prescribes the medication of his/her patients, constitutes a cluster. GPs were recruited as subinvestigators from October 2017 until June 2018 from the pool of teaching physicians at the University of Bern and from the group of GPs who attended project presentations hosted by the BIHAM throughout 2017 and 2018. Additional GPs will be recruited throughout 2019 to replace GPs who had to withdraw from the study, as the data export to the FIRE database did not work in their GP office. Engagement with GPs started early in anticipation of slow recruitment, which has been reported in previous studies.^24 25^ All eligible GPs who showed interest in the OPTICA trial were visited by the investigators at their GP office and given a detailed explanation of the trial.^26^ As of July 2019, 83% of the participating GPs are male. Eighty per cent of the GPs work in group practice, while 20% work in single practice. Twenty-nine per cent of GPs work in the countryside and 71% work in urban and suburban areas.

### Randomisation

Randomisation is done after the cluster has been completed. The randomisation is done centrally in a web-based system (REDCap) by a study team member after all cluster information has been entered. Each participating GP is allocated 1:1 to the intervention group or the control group, using unstratified randomisation with a random sequence of block sizes of two and four. An independent statistician, who is otherwise not involved in the trial, generated the randomisation list. To uphold the concealment of allocation only system administrators who are otherwise not involved in the trial can access the randomisation list.

### Eligibility criteria

#### Inclusion criteria

##### GP level

To be eligible for participation, GPs must be participating in the ‘Family medicine ICPC Research using Electronic medical records’ (FIRE) project led by the Institute of Primary Care of the University of Zurich.^27^ The EMR they use in their GP office have to be compatible with the FIRE database, which is a database with anonymous data from the EMR of more than 500 GPs in Switzerland. The database of the FIRE project contains administrative data, vital data, laboratory values, International Classification of Primary Care 2 (ICPC-2) codes for diagnoses and information on medications prescribed. Participating GPs can, only for the purpose of this trial, identify individual patients in the usually anonymous FIRE database, so that their data can be used in this trial. All participating GPs must complete an online training for Good Clinical Practice (GCP).

##### Patient level

Patients must be enlisted by one of the participating GPs, so that this GP is their main prescribing physician and they must see their GP regularly. The investigators left the definition of regularity to the judgement of participating physicians. Patients must be ≥65 years of age, have ≥three chronic diseases based on ICPC-2 coding or based on the GP’s clinical decision (multimorbidity), and regularly take ≥five medications (polypharmacy). Written informed consent must be sought from patients or, if patients suffer from cognitive impairment, their relative prior to enrolment. This consent includes the right to obtain data from the FIRE project about the study participant.

#### Exclusion criteria

##### GP level

In group practices, only one GP can take part in the trial.

##### Patient level

To maximise the generalisability of the study population, the investigators kept exclusion criteria to a minimum. They excluded patients currently taking part in another interventional study.

### Intervention

The intervention, a systematic medication review, includes the use of a web-based CDSS called ‘Systematic Tool to Reduce Inappropriate Prescribing’-Assistant (STRIPA), developed by a team from the Utrecht University and the University Medical Centre Utrecht in the Netherlands.^28^ STRIPA is based on all algorithms of the ‘Screening Tool of Older Person’s Prescriptions’ (STOPP) and ‘Screening Tool to Alert doctors to Right Treatment’ (START) criteria V.2,^29^ which are expert-consensus lists of inappropriate and appropriate medications for older adults that consider coexisting medical conditions and are thus suited for optimising the prescriptions of multimorbid older patients.^30^ STRIPA combines implicit and explicit prescribing tools and takes a stepped approach that actively encourages patient involvement in decision-making.^28 31^ Taking into account medications, diagnoses, laboratory values and vital data, the STRIPA generates recommendations for physicians about ‘underprescribing, ineffective prescribing, overprescribing, side effects, contraindications, (…) drug–drug and drug–disease interactions, incorrect dosages/dosing frequencies and practical intake issues’.^28^ The intervention’s recommendations allow patients and GPs to conduct a shared decision-making process about patients’ medication intake, so patient preferences play an important role in this trial.

A STRIPA validation study with GPs based on two test cases showed appropriate prescribing decisions increased and inappropriate decisions decreased during a medication review of an older, multimorbid patient with polypharmacy.^31^ STRIPA is being tested in the European multicentre clinical trial ‘OPtimising thERapy to prevent Avoidable hospital admissions in Multimorbid older people’ (the OPERAM trial) in the hospital setting to find out if it can reduce drug-related hospital re-admissions.^32^

This study adapted the intervention from the OPERAM trial so it could be tested in the primary care setting.^33^ The intervention comprises six steps:

This data will be imported from the FIRE database into the STRIPA: patients’ baseline characteristics (eg, sex, age); vital data and laboratory measurements (eg, kidney function, blood pressure), patients’ signs and symptoms, different scores (eg, HAS-BLED score for major bleeding risk), ICPC-2 coded diagnoses, and medications entered as Anatomical Therapeutic Chemical codes.GPs log in to STRIPA and see a list with their recruited patients’ identifiers. When they click on a patient’s ID, the information exported from the EMR to STRIPA via FIRE becomes visible (from Step 1). The GP can add unrecorded values or adjust values (eg, when more recent laboratory values are available). This might be necessary because it might take some time to obtain the FIRE data and to import it to STRIPA and hence the information might change in the meantime.GPs use a drag and drop function to link each medication to a diagnosis.GPs run the analysis in STRIPA and then look at STRIPA’s recommendations. After the analysis is finished, STRIPA records the recommendations it generates so that they will be available for later analysis and generates a PDF report that can be saved by GPs.GPs then must decide if they agree with STRIPA’s advice given and if they will present it to their patient. They can follow, partly follow, or decline STRIPA’s recommendations.At the next appointment with the same patient, GPs will present the recommendations that they consider appropriate. GP and patient will decide together, in a shared decision-making process, which recommendations to implement. GPs will work from a checklist that explains how to conduct the shared decision-making process so that the patients’ preferences are met. The shared-decision making process is based on Elwyn *et al*’s model^34^ and was adapted from the OPERAM trial. The four key elements of this shared decision-making process are ‘choice talk’, ‘option talk’, ‘preference talk’, and ‘decision talk’.^34^ Patients may follow, partly follow or decline the recommendations. Because multimorbid patients are likely to have multiple prescribers, GPs and patients can discuss recommendations with other prescribers, for example, specialists. The GP records in the REDCap study database the patient’s decisions and the reasons recommendations were accepted, partially accepted, or declined. These records will be analysed later.

Before the intervention, GPs in the intervention group will watch an instruction video and read training material that will guide them through the intervention step-by-step.

### Sham intervention

Patients assigned to the control arm receive a sham intervention from their GP—a medication discussion in accordance with usual care. This means that the GP will, as usual in standard care, ask the patient if the current list of medication is complete or needs to be adapted, then share decision making with the patient about possible changes. The GPs who do the sham intervention will receive the same shared decision-making checklist as the GPs in the intervention group. The investigators explicitly ask GPs not to deviate from their usual practice when they review the patients’ medication and not to use additional tools. After the sham intervention, GPs record procedures, decisions, and reasons in the REDCap study database for later analysis. This sham intervention ensures that the medication list of control group study participants, which will be used to assess study outcomes, is up-to-date, while also ensuring patients are blinded.

### Screening and enrolment

For patient recruitment, the investigators use data from the FIRE project to prepare a screening list for each GP that contains a random selection of eligible patients. On each screening list, there are about 20 patients who were randomly sampled from all enlisted patients after they met the age criteria and were determined to regularly take at least five chronic medications, based on the Pharmacy-based Cost Group model.^35–37^ Since ICPC-2 coding is suboptimal in many GP offices, the investigators decided not to include the chronic disease criterion when they prepared the screening lists. From the list, GPs systematically recruit eight to 10 patients who meet the full inclusion criteria, which now include the number of chronic diseases, and do not meet any of the exclusion criteria. GPs will recruit patients starting either at the bottom of the list or the top. If GPs have finished the first screening list without recruiting the minimum amount of participants, the investigators will provide them with a second list.

Since the screening lists are compiled from a random patient sample from each GP office based on FIRE data, patients on the list may have been treated by a different GP who works in the same group practice. It is also possible that patients on the list changed their GP or have died. Since prescriptions frequently change,^38^ some patients with polypharmacy might not have qualified for the screening list when data was last exported. For all these reasons, the protocol allows GPs to skip patients on the screening list if they provide an explanation, or to recruit patients who are not on the list but fulfil the inclusion and do not meet the exclusion criteria. After identifying patients on the list and verifying their eligibility, GPs then inform the patient about the study and seek their informed consent. Study-related appointments are added to the patients’ regular appointments at no charge.

### Data collection

Study participants or their relatives are followed up by phone at baseline and at 6 and 12 months after study enrolment to collect data. At these times, complementary information from the FIRE database, including information about medications and chronic diseases, is imported into the REDCap study database.^27^

### Blinding procedures

The OPTICA trial is blinded to the extent the cluster design of this RCT allows. The method of partial blinding, which is similar to that used in the OPERAM trial,^32^ is set out in detail in table 1.

**Table 1 T1:** Blinding status and measures to assure blinding

Role	Blinding status	How to achieve blinding
General practitioners	Unblinded	When screening for patients and seeking informed consent, GPs are still blinded, as each cluster (GP) will be only randomised after the cluster is full (8–10 patients). The screening list GPs use for recruitment contains a random sample of potentially eligible patients, which was generated from FIRE data by a blinded study team member. All this is done to prevent selection bias. However, since GPs can recruit patients outside this list, not all study participants are recruited randomly. However, the study design makes it impossible to blind GPs throughout the trial. When GPs do the medication review/discussion, they know what group they are allocated to. Nevertheless, GPs in the control arm do not know the procedures in the intervention arm, which prevents cross-contamination; if they knew the procedure in the intervention arm, they might adapt their usual care.
Data collectors and assessors	Blinded	The randomisation of GPs is kept concealed from the team that makes follow-up calls to avoid interviewer bias. Data collectors and assessors have no access to unblinded study information in the database or to local source data. If a SAE occurs, the study coordinator and project manager will be informed.
Data manager and data analyst	Unblinded	The investigators cannot blind the data managers and analysts because they can see the differences in data structure between the study groups. This is why the investigators will use a new data analyst to prepare a clean data set with truncated data to conduct a blinded analysis of the primary outcome.
Study coordinator and project manager, including principal investigator	Unblinded	The study coordinator, project manager and the principal investigator of the trial know the treatment allocation. They are responsible for collecting information about SAEs and performing safety assessments.
Patients	Partially blinded	Patients stay partially blinded. They are only given a ‘high-level description’ of the study question so they know that their GP has been allocated to one of two study groups, but they do not know which one. To uphold patient blinding, patients in the control group will meet their GP for a medication discussion and a shared decision-making about their prescriptions. This means patients in each study arm see GPs the same number of times during the trial and cannot guess their allocation status based on the number of consultations.

The OPTICA trial’s approach to blinding resembles the approach used in the OPERAM trial.^32^

GP, General Practitioner; OPERAM, OPtimising thERapy to prevent Avoidable hospital admissions in Multimorbid older peopl; OPTICA, Optimising PharmacoTherapy In the multimorbid elderly in primary CAre; SAE, serious adverse event.

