The following secondary outcome is assessed at baseline only:

Patients’ willingness to have medications deprescribed, measured with the validated ‘revised Patient Attitudes Towards Deprescribing’questionnaire^47 48^ (patient/relative phone call).

Safety outcomes include adverse events, serious adverse events and device deficiencies.

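### SAEs are worked up and assessed by staff who know the arm, and the blinded analysis stops at the primary outcome although blinded callers already collect falls, fractures and hospitalisations

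*Protocol article*

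**What the plan says.** Four parts of the protocol article bear on this.

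- **Unblinded trial leadership (Table 1).** "The study coordinator, project manager and the principal investigator of the trial know the treatment allocation". The same row adds: "They are responsible for collecting information about SAEs and performing safety assessments".
- **Blinded collectors and assessors (Table 1).** "Data collectors and assessors have no access to unblinded study information in the database or to local source data". This row also contains the hand-over: "If a SAE occurs, the study coordinator and project manager will be informed".
- **Data managers and analysts (Table 1).** They are listed as unblinded, with a reason: "The investigators cannot blind the data managers and analysts because they can see the differences in data structure between the study groups". The remedy is a new analyst, "to prepare a clean data set with truncated data to conduct a blinded analysis of the primary outcome". No other outcome is named.
- **Outcomes and sources.** Under Follow-Up, a blinded team member makes the calls at baseline, 6 and 12 months. Under Assessment of secondary outcomes, falls, fractures, emergency room visits and planned and unplanned hospitalisations come from those calls, and survival from the call or the GP. The section closes: "Safety outcomes include adverse events, serious adverse events and device deficiencies".

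**The concern.** The primary outcome rates prescribing. The Discussion concedes that it does not measure something patients feel directly, and the Ethics section asserts that participants face no more risk than in standard care. Evidence on that assertion has to come from clinical events and safety data, which receive less blinding than the MAI and AOU.

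Two steps are open. First, whether an event counts as serious, and above all whether it is related to a medication change, calls for judgement, and Table 1 has that judgement made with the arm known. Relatedness is also lopsided: only intervention patients have a STRIPA recommendation to which an event could be attributed. Second, outside the primary outcome the analyst knows the arm when choices are made about derivation, missing data or adjustment. A report of no additional harm would then lack a protection that the efficacy result has.

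**Working it through.** The article gives no figure to reproduce here, so the check sets out, for each outcome, who does what.

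| Outcome | Ascertained by | Classified by | Analysed |
|---|---|---|---|
| MAI, AOU | FIRE data | blinded assessors | blinded, truncated data set |
| Falls, fractures | blinded caller, both arms | no relatedness filter described | no blinded analysis named |
| Hospitalisations, emergency visits | blinded caller, both arms | no relatedness filter described | no blinded analysis named |
| Survival | blinded caller or unblinded GP | little judgement needed | no blinded analysis named |
| SAEs | may surface in blinded calls; information then collected by unblinded staff | unblinded staff | no comparison described |
| Device deficiencies | software used in one arm only | not comparable between arms | not comparable between arms |

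**Step 1, ascertainment.** For falls, fractures and hospitalisations the caller does not know the arm, the patient is partially blinded, and the questions and time points are listed once for both arms. This step is largely protected. Survival is partly GP-reported, but whether a patient has died leaves little room for opinion.

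**Step 2, SAE classification.** The notification sentence stands in the blinded collectors' row, so some SAEs plausibly first come to light in a blinded call. After that, work-up and assessment pass to people who know the allocation. No blinded classification is described at any point.

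**Step 3, analysis.** The blinded analysis is named for the primary outcome only. All other outcomes fall under the general statement that managers and analysts are unblinded.

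**Step 4, does the stated reason reach these outcomes?** The reason is that data structure differs by arm. For some outcomes it clearly could. The share of STRIPA recommendations accepted exists in one arm only, and the cost outcome includes GP time on the intervention and software costs. For falls, fractures, hospitalisations and survival the article states no difference by arm in items, timing or source. An extract with those variables, a masked arm code and recoded GP identifiers would have the same structure in both arms. The article already plans an extract of this kind for the MAI and AOU.

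**Step 5, can the bias be sized?** Not from this document. Suppose a share *f* of one arm's *n* events is added or removed by biased classification when the true ratio is 1. The observed ratio becomes n(1 ± f)/n = 1 ± f. The event count cancels and the answer is simply the assumed *f*, for which the article offers no basis. Reclassifying relatedness alone would leave an all-cause count unchanged.

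**The case against.** The strongest reply is that this is an openly disclosed design choice in a trial where GPs cannot be blinded. Clinical events are already ascertained blind, are secondary outcomes in both arms, and have stated model types under Statistical analysis. An analyst cannot turn a fall recorded by a blinded caller into something else. The article describes no between-arm test of adverse events or SAEs, and nothing says that relatedness enters a comparison; such detail commonly sits in a full protocol or analysis plan, which is not shown. An independent Safety and Data Monitoring Board meets regularly, and safety reporting follows Swiss law.

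Most of this stands, and it limits the point. It does not answer the two things Table 1 states outright: safety assessment by unblinded staff, and a blinded analysis restricted to the primary outcome. The board is described as discussing safety, not as classifying events.

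Three stronger readings are tempting and are not supported:

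- A reader might infer that SAEs are collected only by people who know the arm. The blinded calls and the notification sentence in the blinded row speak against that.
- A reader might infer that existing blinded staff could remove the bias by classifying SAEs. Those staff are kept away from local source data, and SAE narratives are likely to mention medication changes. Using the MAI and AOU raters could unblind the co-primary outcomes. GPs would remain unblinded in any case.
- A reader might attach a shifted rate ratio to the problem. As Step 5 shows, that would only restate an assumption.

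**Conclusion.** The point holds in limited form. SAE work-up and classification are unblinded with no blinded classification described. The blinded analysis stops at the primary outcome for a reason not shown to apply to the phone-collected events. The remaining exposure is SAE judgement, GP reports and analyst choices on falls, fractures, hospitalisations and survival.

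Its size cannot be quantified from the article and is probably modest for the phone-collected events, whose ascertainment is already blind. It is larger in principle for relatedness, should that be compared between arms. The co-primary results are not affected. The conclusion assumes that the calls use the same questions in both arms, as the outcome list implies, and that no unseen plan already widens the blinded analysis.

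**What to change.** 1. Amend the analyst row of Table 1 so that the clean truncated data set and the blinded analysis also cover falls, fractures, hospitalisations and survival, with a masked arm code and recoded GP identifiers.
2. State that any between-arm conclusion on harm will rest on these all-cause outcomes, and that relatedness judged with knowledge of the arm will be reported descriptively only.

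The cost is a few more variables for the new analyst to prepare and some wording. Regulatory SAE reporting by the unblinded team does not change, and the MAI and AOU raters should not be asked to classify SAEs. On the article's timetable, with last patient out expected in the second half of 2020, the change can be made before the final analysis.

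What it does not cure: GP reporting stays unblinded, and device deficiencies arise in one arm only, so they can be described but not compared.
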